### Screening, eligibility assessment, and recruitment

Retrospective cohort for model development: Site ED records will be screened for potential cases of bone and joint infection by the local clinical team. ED attendance codes/keywords including, but not limited to, any of the keywords ‘limp, limping child, abnormal gait, osteomyelitis, septic arthritis, swollen leg/joint, non-weightbearing, limb and joint pain, transient synovitis’ will be reviewed. These predefined attendance codes and keywords were derived during the feasibility study, but additional keywords can be identified and added by the participating centres. If the ED record indicates bone and joint infection as a differential diagnosis, the electronic patient record will be reviewed. Patient medical records, which include their admission and progress notes, operation notes, discharge summaries, and imaging reports will be scrutinized.

Prospective cohort (18 months recruitment – three months’ follow-up) for model validation: Similar to the retrospective cohort, patients with suspected bone and joint infection will be identified in participating centres either in the ED, on admission, or in the paediatric or paediatric orthopaedic department. Patients will be recruited when the treating clinician believes that the child may have a diagnosis of bone and/or joint infection (i.e. bone and joint infection is part of the differential diagnosis, even if the treating clinician believes it can be effectively ruled out based on the history and examination alone). At three months post recruitment, information pertinent to defining the reference standard will be collected. Any complications will be recorded. The DINOSAUR study demonstrated that the diagnosis of osteomyelitis can be reliably determined by three months.^7^ Families of children discharged from hospital without a definitive diagnosis will be contacted by text message, phone, or email at three months from recruitment to confirm complete resolution of symptoms and ensure they were not treated in a different hospital. The patient flowchart (prospective cohort only) is shown in Figure 1.

**Fig. 1 F1:**
[figure not shown]
Patient flowchart (prospective cohort).

Qualitative study: The qualitative study will run in approximately 15 of the sites involved in the prospective cohort study and explore the perspectives of children/young people, parents/carers, and health professionals on the diagnostic process for bone and joint infection. Participants from the prospective cohort will be invited to participate in this sub-study.

We will conduct semi-structured qualitative interviews with a purposive sample of approximately 20 families, sampling for diversity in terms of study site, child age, ethnicity, and family socioeconomic status, and include patients with experience of USS, MRI, or both. The sample will mainly comprise those diagnosed with bone and joint infection, but we will also interview a sub-set of patients/families who have undergone investigations for suspected bone and joint infection but received other diagnoses. The perspectives of these two groups may differ in important ways, and it is important that clinical practice is informed by both groups. Sampling of families will also be informed by the concept of information power,^11^ and the ongoing data analysis.

### Sample size considerations

Sample size for retrospective cohort to estimate the diagnostic accuracy: For the primary objective, we will collect retrospective data for an estimated sample of 6,000 children with suspected bone and joint infection. Based on our feasibility data, approximately 444 (7.4%) would have confirmed bone and joint infection and 5,556 (92.6%) would be disease-free. Based on our pilot study, this would provide data for approximately 351 (79%) MRI disease cases and 408 (92%) USS disease cases, allowing MRI sensitivity to be estimated to within 2.9 percentage points of 91.5% and USS sensitivity to be estimated to within 4.3 percentage points of 74.1% with 95% confidence. This would also provide 611 (11%) MRI and 1,000 (18%) USS disease-free cases, allowing specificity to be estimated to within 3.7 percentage points of 67% for MRI and within 3.1 percentage points of 47% for USS with 95% CI.

Sample size for retrospective cohort to develop the diagnostic prediction model: We will develop two diagnostic prediction models to predict bone and joint infection; one for children aged under five years (Model 1) and one for children aged five years and older (Model 2).

In the retrospective cohort, we anticipate that there will be 1,440 children aged under five years, of whom 107 have a bone and joint infection for Model 1, and 4,560 children aged five years and older, of whom 348 have a bone and joint infection for Model 2. This is based on the estimate that 24% of children with confirmed bone and joint infection will be aged under five years (NHS Digital 2017/18).^14^

Using this information and to minimize the risk of overfitting and to precisely estimate the overall outcome risk, we calculated that ten predictors can be examined for inclusion in Model 1 and 32 predictors can be examined for inclusion in Model 2. This is based on a conservative estimate of the anticipated R^2^ of 0.15*max(R^2^) (max R^2^ = 0.41 for an anticipated outcome prevalence of 0.074).^15^

We have since updated the sample size calculation during data collection based on changes in the prevalence of bone and joint infection from 7.4% to 5.3% for Model 1 and to 7.6% for Model 2 (change made 9 October 2024). With the current record of the retrospection cohort, there are 3,426 children aged under five years, of whom 180 have bone and joint infection (Model 1), and 2,314 children aged five years and older, of whom 177 have bone and joint infection (Model 2). Based on a conservative estimate of the anticipated R^2^ of 0.15*max(R^2^) (max R^2^ = 0.41 for an anticipated outcome prevalence of 0.053 and 0.076), 19 predictors can be examined for inclusion in Model 1 and 16 predictors can be examined for inclusion in Model 2.

Sample size for prospective cohort to evaluate the performance of the diagnostic prediction model: For an external validation study, it was recommended that there are at least 100 events (i.e. instances of bone and joint infection) to evaluate the discrimination and the calibration of the developed model in an independent sample.^16^ The DINOSAUR study recruited at least one child admitted with suspected bone and joint infection from each centre every month.^7^ We therefore plan to recruit 111 patients from at least 30 centres over 18 months to meet the required sample size.

However, since planning this study, new sample size guidance for external validation studies has become available.^17^ Using this new guidance and the updated prevalence estimates for bone and joint infection, we base our sample size calculation using the anticipated c-statistic by the max Nagelkerke’s R^2^ and assume a 5.3% and 7.6% of event rates for Model 1 and Model 2, respectively (change made 20 November 2024). We use 15% of the max R^2^ which equates to ~ 0.05 (Model 1) and 0.06 (Model 2) given the assumed outcome prevalences, and we base our sample size on estimating a c-statistic of ~ 0.77 (Model 1) and 0.75 (Model 2) with targeted a standard error of 0.038. This corresponds to a CI of width 0.15, meaning we would need a sample size of 751 children aged under five years, of whom 40 have a bone and joint infection (Model 1), and 575 children aged five years and older, of whom 44 have a bone and joint infection (Model 2) for external validation.

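### The sensitivity precision for the primary objective still assumes 444 cases, although the October 2024 update reports 357 for the same cohort; expected half-widths are about 3.3 (MRI) and 4.7 (USS) points, not 2.9 and 4.3

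*Protocol article*

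**What the plan says.** The first paragraph of Sample size considerations in the Protocol article deals with the primary objective, the diagnostic accuracy of MRI and USS. It starts from the planned size, "we will collect retrospective data for an estimated sample of 6,000 children with suspected bone and joint infection", and the expected split, "approximately 444 (7.4%) would have confirmed bone and joint infection and 5,556 (92.6%) would be disease-free". Pilot imaging rates then give the number of cases with each test: "this would provide data for approximately 351 (79%) MRI disease cases and 408 (92%) USS disease cases". From these the article states the precision for the two sensitivities: "allowing MRI sensitivity to be estimated to within 2.9 percentage points of 91.5% and USS sensitivity to be estimated to within 4.3 percentage points", the anticipated USS value being 74.1%. For specificity it gives 611 MRI and 1,000 USS disease-free children, with half-widths of 3.7 points around 67% and 3.1 points around 47%.

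Later in the section, the update dated 9 October 2024 reports the record as it then stood, by model. For the younger group it says "there are 3,426 children aged under five years, of whom 180 have bone and joint infection (Model 1"). The entry for the older group reads "2,314 children aged five years and older, of whom 177 have bone and joint infection (Model 2"). From these counts the article revises the number of candidate predictors to 19 and 16. A further change, dated 20 November 2024, uses the revised prevalences of 5.3% and 7.6% for the external validation sample. No revised precision is given for MRI or USS accuracy.

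**The concern.** Both sets of figures describe the same retrospective cohort. The update replaces the prevalence and case counts for the prediction models but leaves the accuracy paragraph on the old count. Sensitivity is estimated only in confirmed cases, so its precision depends directly on the number that has fallen from 444 to 357. A reader who takes the section as the current plan sees an expected precision for the primary objective that the article's own later counts no longer support. At stake is the accuracy of a stated planning figure; no analysis or design choice depends on it.

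**Working it through.** **Inputs, all from Sample size considerations.** Planned: 6,000 children, 444 cases, 5,556 disease-free. Imaged among cases: MRI 79%, USS 92%. Imaged among disease-free: MRI 11%, USS 18%. Anticipated sensitivity: 91.5% and 74.1%. Anticipated specificity: 67% and 47%. Updated record: 3,426 children with 180 cases, and 2,314 with 177.

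**Formula.** 95% half-width = 1.96 × √(p(1 − p)/n).

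**Step 1. Reproduce the stated figures.**
- Numbers imaged: 444 × 0.79 = 351; 444 × 0.92 = 408; 5,556 × 0.11 = 611; 5,556 × 0.18 = 1,000.
- MRI sensitivity: 1.96 × √(0.915 × 0.085/351) = 2.92 points (stated 2.9).
- USS sensitivity: 1.96 × √(0.741 × 0.259/408) = 4.25 points (stated 4.3).
- MRI specificity: 1.96 × √(0.67 × 0.33/611) = 3.73 points (stated 3.7).
- USS specificity: 1.96 × √(0.47 × 0.53/1,000) = 3.09 points (stated 3.1).

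All four reproduce, so this is the article's own method.

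**Step 2. Updated counts.** Children: 3,426 + 2,314 = 5,740. Cases: 180 + 177 = 357, or 6.2%. Others: 5,740 − 357 = 5,383.

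**Step 3. Same formula, pilot shares and accuracy unchanged.**

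| Measure | n | Half-width (points) | Stated |
|---|---|---|---|
| MRI sensitivity | 357 × 0.79 = 282 | 3.25 | 2.9 |
| USS sensitivity | 357 × 0.92 = 328 | 4.74 | 4.3 |
| MRI specificity | 5,383 × 0.11 = 592 | 3.79 | 3.7 |
| USS specificity | 5,383 × 0.18 = 969 | 3.14 | 3.1 |

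Wilson intervals give 3.28 and 4.72 for the sensitivities, so the choice of interval does not matter. The specificity rows treat every non-case as disease-free, although the reference standard also defines an uncertain group.

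**Step 4. Record completed to 6,000 at the observed prevalence.** 6,000 × 357/5,740 = 373 cases. MRI: n = 295, ±3.18. USS: n = 343, ±4.63. Reaching 444 cases would take about 444/0.0622 ≈ 7,140 children.

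**Step 5. Relative size.** Against the stated figures, the smallest increase is 4.63/4.3 = 1.08 and the largest 3.25/2.9 = 1.12, so the intervals are 8 to 12% wider. From the case counts alone, √(444/357) = 1.115: about 11.5% wider or, seen from the other side, the stated interval is about 10% too narrow (1/1.115 = 0.897).

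**Step 6. Could higher imaging uptake restore the limits?** Allowing for rounding (2.95 and 4.35), the limits need about 343 cases with MRI and 390 with USS. For MRI that is 343/357 = 96% of current cases, or 343/373 = 92% at 6,000, against 79% in the plan. For USS, 390 exceeds both 357 and 373, so no uptake suffices at 74.1% sensitivity.

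**The case against.** The case for leaving the text alone has four parts.

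- **The stated arithmetic is correct, and the paragraph is a projection.** It is explicitly an estimate from feasibility and pilot data, and the section then reports what changed since. That stands. A reader might infer a calculation error or a broken commitment, and neither is supported: the figures reproduce, and the article sets no minimum precision that 357 cases would fail.
- **The 357 is interim, from a record of 5,740 children.** True, but completion to 6,000 at the observed prevalence does not restore the limits (Step 4).
- **The revised widths rest on pilot inputs too.** This also stands. A slightly higher MRI sensitivity would bring back the stated limit: 1.96 × √(0.932 × 0.068/282) = 2.94 points. USS would need about 80%: 1.96 × √(0.80 × 0.20/328) = 4.33 points, a larger departure from 74.1%. The revised figures are expectations under the plan's own assumptions, and the MRI one is the less secure.
- **The article is abridged, and the full working protocol may already hold a restated figure.** That is possible and cannot be checked here. But the article itself states the precision and itself reports the counts that undercut it.

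A reader might also want to extend the point to the two age groups, for which Statistical analysis plans separate estimates. Applying the overall shares to 180 and 177 cases gives about ±4.6 points for MRI and ±6.7 for USS in each group. The article does not support using those figures. They assume equal imaging uptake and accuracy at both ages, while Statistical analysis says most under-fives need sedation or anaesthesia for MRI and older children do not. The Introduction adds that this need affects clinical decisions. Subgroup precision is also something an article may leave to the full protocol or analysis plan.

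**Conclusion.** The point holds for overall sensitivity. The precision given for the primary objective rests on a case count that the article has itself replaced. On its own formula and pilot inputs, the expected half-widths move from 2.9 to about 3.3 points for MRI and from 4.3 to about 4.7 for USS, or to about 3.2 and 4.6 at 6,000 children. Specificity is in effect unchanged, at about ±3.8 and ±3.1.

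A loss of 0.3 to 0.5 points does not put the primary objective at risk, and the planned reporting of 95% CIs will show the precision achieved. The conclusion assumes that the pilot imaging shares (79% and 92%) and sensitivities (91.5% and 74.1%) still apply, because the article gives no newer values.

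**What to change.** Restate the overall sensitivity precision on the updated case count. Where the numbers of cases actually imaged with MRI and USS are known, use them. Otherwise give about ±3.3 and ±4.7 points on the current record (±3.2 and ±4.6 at 6,000) and say that pilot uptake and accuracy are assumed. The specificity figures can be refreshed in the same sentence, to about ±3.8 and ±3.1. Do not insert age-specific half-widths derived from the overall imaging shares; if they are wanted, base them on numbers imaged within each age group.

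The cost is wording only. No extra patients are needed and no analysis changes; the stated precision becomes slightly less favourable.

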### Statistical analysis

Diagnostic test accuracy: For each index test (USS and MRI), the results will be compared to the reference standard among all patients with available data and cross tabulations reported (including indeterminate results). The sensitivity, specificity, negative predictive value, positive predictive value, likelihood ratio, and diagnostic odds ratios will be reported (with 95% CIs) overall, as well as separately for patients aged five years and older versus those aged under five years. This choice was based on our feasibility study finding that most children under the age of five years require sedation or anaesthesia for MRI, while those aged five years and above do not.

Model development and validation: Two models will be fitted using logistic regression: one for children aged under five years and one for children aged five years and older. A single unified model will also be explored. Candidate predictors for both models will be chosen based on clinical plausibility and from a review of the literature. We will select variables for inclusion in the model using least angle selection and shrinkage operator (LASSO) penalties. Continuous predictors will be examined for nonlinear relationship with confirmed bone and joint infection using fractional polynomials.^18^ Missing data will be inevitable with not all patients providing data on all predictors of interest.

To avoid excluding patients when developing and validating our models, we will use multiple imputation to impute missing values, under a missing at random assumption. Identifying the true underlying missing data mechanism from the available data is rarely possible. Assumptions need to be made on the plausible mechanism, and approaches needed to be used. Under a missing at random (MAR) assumption, the missingness after conditioning on the observed data does not depend on the unobserved (unseen) data. Using this approach, we can apply methods such as multiple imputation, by fitting a joint model to the observed data and impute the missing data, taking account of the uncertainty in the estimated parameters of this joint model. MAR is a pragmatic decision, which makes a less strong and more realistic assumptions than a missing completely at random approach and conducting a complete-case analysis. The MAR imputation model will include all variables considered for the multivariable model building, the outcome, and any auxiliary variables (such as centre-specific covariates) that will help explain the missingness.

The internal validity of the final models will also be assessed using bootstrap resampling to adjust for over-optimism in the estimation of model performance.^19^ The internal validation will quantify and be used to adjust the performance measures for any optimism. The performance of the prediction model will be characterized by assessing calibration and discrimination.^20^ Calibration, which reflects how close the predictions from the model are to the observed outcome frequencies, will be assessed graphically, using a calibration plot, plotting observed outcomes against predictions using smoothing techniques. The plot will also be supplemented with results for individuals grouped by similar probabilities (tenths) comparing the mean predicted probability to the mean observed outcome. Calibration will also be quantified by calculating the calibration slope and intercept. The discrimination of the prediction models will be summarized with the concordance index (equivalent to the area under receiver operating characteristic curve) with 95% CI.

External validation: The performance of the two models will also be assessed in the prospective external validation cohort.^21^ Discrimination, calibration, and a decision curve analysis will be evaluated. Any miscalibration identified during this phase will be addressed by recalibrating the model (e.g. re-estimating the intercept or updating the regression coefficients by a common factor).^22^ During the external validation the incremental value of adding USS and MRI to both models will be examined. Missing data will be handled using multiple imputation and model performance measures (concordance index, calibration slope, and intercept) will be pooled using Rubin’s rules.

All statistical analyses will be carried out in R v. 4.4.2 (R Project for Statistical Computing, Austria).

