### Study population

The target population is children and young people aged under 15 years and nine months (aged under 16 years at the end of the three-month follow-up) with a suspected diagnosis of bone and joint infection by the treating clinician. The cohort study will be conducted in NHS secondary care hospitals throughout the UK. The first cohort (retrospective) will be identified through emergency department (ED) records in participating centres. The second cohort (prospective) will also be recruited in ED or acute wards at the same centres. Support from PERUKI and the British Society for Children’s Orthopaedic Surgery (BSCOS)^9^ will help facilitate recruitment and support the study.

We have considered the Innovations in Clinical Trial Design and Delivery for the Under-served (INCLUDE) guidance in preparing the study.^10^ Diversity is particularly important, as diseases which appear more frequently in different racial or ethnic groups may affect the diagnostic process of bone and joint infection (e.g. sickle cell disease, haemophilia). Furthermore, there is evidence that the incidence of bone and joint infection increases with increasing socioeconomic deprivation.^11^ In discussion with our Patient and Public Involvement co-investigators, we will be targeting hospitals covering under-served and ethnically and racially diverse areas (e.g. East London, Birmingham) to ensure our sample is inclusive.

The main inclusion and exclusion criteria for the trial are summarized in Table I.

**Table I. T1:** Inclusion and exclusion criteria.

Inclusion criteria	Exclusion criteria
Age 0 to 15 years	There is evidence that the patient and/or parent/guardian would be unable to adhere to study procedures or complete follow-up
Bone and joint infection is part of the differential diagnosis, even if the treating clinician believes it can be ruled out on the basis of history and examination alone	Limited comprehension by the parent/guardian of the English language
Duration of symptoms < two weeks at the time of attendance to acute healthcare	Suspected infections affecting the axial skeleton (skull, spine, or ribs)
Symptoms affecting the appendicular skeleton only	Traumatic aetiology of symptoms

We have established the feasibility of reliable retrospective data collection through a pilot study.

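### As written, the external validation describes performance in fully tested children only; performance with predictors missing and the outcome unknown is not planned for

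*Protocol article*

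**What the plan says.** The missing-data text under Statistical analysis gives imputation a double purpose: "To avoid excluding patients when developing and validating our models, we will use multiple imputation to impute missing values". It describes a single imputation model under MAR: "The MAR imputation model will include all variables considered for the multivariable model building, the outcome, and any auxiliary variables".

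The External validation paragraph returns to the subject in one sentence: "Missing data will be handled using multiple imputation and model performance measures (concordance index, calibration slope, and intercept) will be pooled using Rubin’s rules". It neither repeats nor changes the content of the imputation model. It also plans a decision curve analysis.

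The same section expects gaps: "Missing data will be inevitable with not all patients providing data on all predictors of interest". No rate is given. Table I under Study population admits children for whom infection is in the differential diagnosis "even if the treating clinician believes it can be ruled out on the basis of history and examination alone", and the recruitment section says the same of the prospective cohort. The article does not say whether a child with a missing predictor would be given a prediction in practice, or by what rule.

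**The concern.** Keeping the outcome in the imputation model is correct when coefficients are being estimated. At validation it does something different: the missing value is drawn partly from the infection status against which the prediction is then scored. The clinician using the tool does not have that information.

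The choice matters because some validation children may have had few tests. If so, the c-statistic, calibration and net benefit from the planned analysis answer how the model performs once everything has been measured. They do not answer how it performs in a child at first presentation whose blood result, say, is absent. The take-home message presents the tool as help for non-specialists at first contact, so a reader could apply the reported figures to the second situation without noticing that they belong to the first.

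**Working it through.** **1. The plan's own precision figure.** Inputs from Sample size considerations: c = 0.77 and prevalence 0.053 (Model 1); c = 0.75 and prevalence 0.076 (Model 2); interval width 0.15, so the target SE is 0.15 / (2 × 1.96) = 0.0383. Newcombe's formula is

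SE² = c(1−c)[1 + (n/2−1)(1−c)/(2−c) + (n/2−1)c/(1+c)] / [n²p(1−p)].

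- Model 1, n = 751: 0.1771 × (1 + 70.03 + 162.92) / 28,308 = 0.001464, so SE = 0.0383.
- Model 2, n = 575: 0.1875 × (1 + 57.30 + 122.79) / 23,218 = 0.001462, so SE = 0.0382.

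Both stated sample sizes reproduce. The planned SE, stated as 0.038, is the yardstick below.

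**2. What the two analyses estimate.** The documents give no missingness rate, so the size was simulated (200,000 children) under assumptions. Event rates and c are close to the plan's. One laboratory-type predictor is missing in 10 to 70% of children, either completely at random (MCAR) or depending on examination findings (MAR). The effect sizes are also assumed. Two treatments of the same gaps are compared: imputation with the outcome, and a deterministic fill from the other predictors without the outcome.

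Model 2, complete-data c = 0.748:

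| Missing | Mechanism | With outcome | Filled without outcome | Gap |
|---|---|---|---|---|
| 10% | MCAR | 0.748 | 0.741 | 0.007 |
| 10% | MAR | 0.748 | 0.744 | 0.004 |
| 30% | MCAR | 0.748 | 0.730 | 0.018 |
| 30% | MAR | 0.747 | 0.734 | 0.013 |
| 50% | MCAR | 0.746 | 0.716 | 0.030 |
| 50% | MAR | 0.749 | 0.722 | 0.027 |
| 70% | MCAR | 0.746 | 0.704 | 0.042 |
| 70% | MAR | 0.744 | 0.706 | 0.038 |

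For Model 1, complete-data c is about 0.760. Imputation with the outcome gives 0.756 to 0.760 throughout. The fill without the outcome gives 0.752 to 0.755 at 10% missing and 0.713 to 0.717 at 70%.

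A second, separate simulation agreed: 0.754 to 0.768 with the outcome against 0.761 to 0.767 with complete data, and a gap of about 0.005 at 10% missing and 0.03 to 0.04 at 50 to 60%.

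**3. Reading the result.** Imputation with the outcome stays at the complete-data value whatever the missingness, so it recovers fully tested performance. The other column falls as missingness rises. In units of the planned SE, the gap is 0.005 / 0.038 = 0.13 at 10% missing, and from 0.03 / 0.038 = 0.8 to 0.05 / 0.038 = 1.3 at 50 to 70%.

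**4. Why the fill should be deterministic.** Random imputation without the outcome adds noise to the predictor. For Model 2 at 70% missing it gave c of 0.668 (MCAR) and 0.675 (MAR), with calibration slopes of 0.64 and 0.69. The deterministic fill gave 0.704 and 0.706, with slopes of 0.97 and 0.94. Random draws would therefore understate what a sensible bedside rule can deliver.

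**The case against.** The strongest reply is that this is a choice of target and not an error. Under MAR, outcome-inclusive imputation estimates performance with all predictors measured, and a clinician can reach that performance by doing the tests. This stands. A reader might infer that the planned figures are inflated or unattainable; the simulations show no inflation against complete data, and the documents do not support that reading.

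Second, the article does not say that predictions will be issued with predictors missing. It does not list the predictors, and Table I does not say that clinically excluded children go untested; the Introduction calls blood tests and radiographs typical work-up. This also stands. It is why the size is given as a range, and why the choice of headline analysis cannot be settled from the article.

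Third, use of the outcome at external validation is inferred. The imputation sentence sits with model development, where validating could mean the bootstrap, and the article calls itself abridged, so the full protocol or SAP may separate the two uses. This stands in part. However, the article does describe one model for both purposes, and its external validation paragraph offers no alternative.

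Fourth, the gap may be small. With modest missingness it is. Larger gaps can also be produced by letting testing follow unrecorded suspicion, but that breaks MAR and is a separate problem, so it is not counted here.

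**Conclusion.** The point holds as a limit on what the planned validation can show. It is not a bias in the planned estimate. The outcome-inclusive analysis is valid for fully tested children under MAR with an adequate imputation model. It gives no information on performance when a predictor is absent and the outcome unknown, and the validated population may contain such children. How far the two differ depends on a missingness rate that the article does not give: negligible beside the planned standard error at about 10% missing, comparable with it at 50 to 70%. These sizes rest on one missing laboratory-type predictor and assumed effect sizes.

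A reader might go further and infer that the imaging increment would be exaggerated. The article says "During the external validation the incremental value of adding USS and MRI to both models will be examined", and expects "approximately 351 (79%) MRI disease cases and 408 (92%) USS disease cases" but scans in only 11% (MRI) and 18% (USS) of disease-free children. If those rates carried over to the planned 84 cases and 1,242 disease-free children, MRI would be missing in 1 − (0.79 × 84 + 0.11 × 1,242) / 1,326 = 85%. The article does not say that scans never performed will be imputed, and it restricts the accuracy analysis to patients with available data. That stronger claim is not supported and forms no part of this point.

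**What to change.** In the missing-data and External validation text of Statistical analysis:

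- Keep the outcome in the imputation model for development.
- Keep outcome-inclusive imputation at validation, labelled as performance in fully tested children.
- Add beside it a validation analysis in which missing predictors are filled by a deterministic rule, such as the conditional mean given the observed predictors, fitted in the development cohort without the outcome and fixed before the validation data are scored. Report the c-statistic, calibration slope and intercept, and net benefit.
- State the intended use, that is, whether the tool may be applied with predictors missing, and let that decide which analysis is the headline.

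The cost is one further analysis of data already being collected. The figures for the missing-predictor setting will probably be slightly less favourable.
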